# Effects of Unfiltered Cigarettes on Smoking Behavior and Toxicant Exposure: Protocol for a Randomized Crossover Clinical Trial

**DOI:** 10.2196/19603

**Published:** 2020-12-08

**Keywords:** nicotine, tobacco, topography, exposure, policy, environmental

## Abstract

**Background:**

Plastic filters on cigarette butts are a widespread source of nonbiodegradable, toxic environmental waste. State and local legislation to ban the sale of single-use cigarettes may be considered to prevent this waste, but scientific evidence on the impact of switching smokers to unfiltered cigarettes on smoking behavior and toxicant exposures is needed to inform this policy. We have designed an open-label, randomized, 9-week, crossover clinical trial of adult filtered-cigarette smokers who switch to unfiltered cigarettes.

**Objective:**

Our objective is to understand the impact of switching smokers of filtered cigarettes to unfiltered cigarettes on smoking behavior and toxic exposures.

**Methods:**

This trial involves a 1-week baseline period; a 2-week period of smoking filtered or unfiltered cigarettes, where groups are randomly assigned; a 3-week washout period; another 1-week baseline period; and a 2-week crossover period of smoking the opposite condition (ie, filtered or unfiltered cigarettes) for a sufficient sample size of 40 participants. We will determine changes in (1) observed topography (ie, puff count, interpuff interval, and puff volume) and cigarettes smoked per day, via butt counts and self-report, (2) expired carbon monoxide and excretion of urinary cotinine, 4-(methylnitrosamino)-1-(3-pyridyl)-1-butanol, and volatile organic compounds, and (3) participants’ knowledge and attitudes toward unfiltered cigarettes, satisfaction with smoking, and intention to quit if they were not able to smoke filtered cigarettes.

**Results:**

This study was funded in June 2018 and approved by the relevant Institutional Review Boards in July 2018. This study has enrolled 37 participants as of October 2020. Data analysis is currently underway, and trial results are expected to be published in spring 2021.

**Conclusions:**

This pilot proof-of-principle study will inform the design of a larger, future research project that can provide robust scientific evidence on our research question. Such a large study could inform possible state or local legislation to ban the sale of single-use filtered cigarettes in order to mitigate the environmental impact of discarded single-use plastic filters.

**Trial Registration:**

ClinicalTrials.gov NCT03749876; https://clinicaltrials.gov/ct2/show/NCT03749876

**International Registered Report Identifier (IRRID):**

DERR1-10.2196/19603

## Introduction

### Background and Rationale

Cellulose acetate (ie, plastic) filters on cigarette butts are a widespread source of nonbiodegradable environmental waste that may be toxic to marine organisms, aquatic environments, and possibly to human and animal health [1-4]. Cigarette butts are, in fact, a major littered item found during beach and urban cleanups each year throughout the world and adversely affect storm water drainage, beaches, neighborhoods, and other natural environments [5]. There is a widespread perception among smokers and nonsmokers that filters provide a *safer* cigarette [6]. In response to the expanding evidence in the 1950s regarding risks for lung cancer and other serious illnesses due to smoking, the tobacco industry sought to address or at least obfuscate these risks through the development of cigarette *filters*. This terminology suggested purification or reduction of smoking risks to the consumer [6]. It is clear that consumers responded to the marketing blitz around filters and the perceived risks of smoking such that today more that 99% of commercially sold cigarettes in the United States are filtered [7].

Most smokers and nonsmokers do not know that the filters attached to almost all cigarettes sold in the United States are made of nonbiodegradable plastic. In addition, cigarette filters have also been deemed “unproved in reducing harms to the average smoker” by the US Surgeon General and the National Cancer Institute [7,8]. Data comparing the relative risks of smoking among age-matched cohorts of smokers across 50 years show that overall mortality, as well as the smoking-attributable risks for morbidity and mortality from lung cancer, heart disease, and chronic obstructive pulmonary disease, increased over the years during which filters became standard issue as part of manufactured cigarettes [9,10]. State and local governments have jurisdiction to ban the sale of various tobacco products, and in 2019-2020, the California Assembly considered, for environmental reasons, a bill to ban the sale of single-use filtered cigarettes [11]. Additional scientific evidence on the human consequences of removing single-use filters from cigarettes is needed to understand what, if any, health and behavioral impacts may result from a sales restriction to eliminate cellulose acetate–filtered cigarettes from the tobacco market.

### Study Objectives

This is a pilot study that will inform a possible larger clinical trial. The research question for the overall project is as follows: *What is the impact of switching smokers of filtered cigarettes to unfiltered cigarettes on smoking behavior and toxic exposures?* The specific aims are as follows:

Determine smokers’ satisfaction and attitudes toward smoking cigarettes if they were to switch from smoking filtered to unfiltered cigarettes.Measure changes in smoking topography (ST) (ie, puff count and puff volume) and cigarettes smoked per day, via butt counts and self-report, among smokers who change to unfiltered cigarettes for 2 weeks compared with these measures while smoking filtered cigarettes.Measure changes in urinary cotinine, 4-(methylnitrosamino)-1-(3-pyridyl)-1-butanol (NNAL), and volatile organic compound (VOC) excretion among smokers who smoke unfiltered cigarettes for 2 weeks compared to smoking filtered cigarettes.

Study results may inform proposed state or local legislation to ban the sale of single-use filtered cigarettes in order to eliminate the environmental impact of improperly discarded, poorly degradable plastic cigarette filters as toxic waste.

### Overview and Trial Design

While the risks of smoking any type of tobacco product are now clear to the public, there has never been a clinical trial comparing changes in biochemically measured exposures, perceptions, topography, and other behavioral elements of cigarette smoking when switching from filtered to unfiltered cigarettes (ie, there have been no studies reported in PubMed or ClinicalTrials.gov as of October 2020). If large-scale trials were needed to definitively answer concerns that policy makers, smokers, and the general public have regarding any potential adverse effects of eliminating filtered cigarettes from the market, it would be important to ascertain the practicality and validity of measures used for such trials. General perceptions of filtered cigarettes and their safety, palatability, and composition have been measured through national panel surveys (publication in progress), but actual changes among smokers switching between filtered and unfiltered cigarettes can only be measured in a clinical trial. Further, to eliminate exposure bias, a trial in which the order of exposure is randomized is most appropriate.

We have completed an open-label, randomized, 9-week, two-sequence, two–treatment condition, crossover clinical trial of 37 adult filtered-cigarette smokers who switch to unfiltered cigarettes. We will evaluate this pilot study’s approach as to its applicability for a follow-up research project with a larger sample size.

This approach uses a crossover design, which allows participants to be their own matched control, hence removing participant-level variability [12]. Cigarette smoking is the *chronic* condition in this trial that persists throughout the washout periods, with changes measured against the chronic condition, not against a nonsmoking condition. This design is often used in clinical trials particularly when evaluating interventions to treat or control chronic diseases such as asthma, for which there is large variability across measures within participants. In this pilot trial, we are measuring changes in smoking behavior due to changes in the product smoked, while not assuming any change in the underlying condition of smoking; this study design then accounts for participant-specific variability. Participants were instructed to resume pretreatment activity (ie, smoking filtered Camel or Pall Mall cigarettes) during the washout period during which there were no study measurements. We assumed 3 weeks to be sufficient to *wash out* the effect of exposure to the study cigarettes during the active treatment period [13].

We collected behavioral data via validated computer-based surveys at baseline, intervention, and postintervention time points to assess changes in knowledge and attitudes regarding smoking of filtered and unfiltered cigarettes. We used a handheld smoking device, the Clinical Research Support System (CReSS) Pocket (Borgwaldt KC), to measure ST over five, daily, 8-hour periods per week; participants took home the device, and measurements were recorded in a naturalistic setting. The rationale for five, 8-hour, ST monitoring periods was based on our aim to measure ST during a representative period for naturalistic smoking. Findings from previous studies using ST measures have not differed between direct and indirect observations [14-16]. Although slightly greater ST variability has been reported between individuals smoking with a CReSS device compared to normal smoking, many studies report consistent within-participant comparisons [14,16,17]. Thus, we were not concerned that smoking outside of the monitoring window would differ from measurement periods. This device enables convenient recording of ST throughout the day and over weeks with time- and date-stamped data; it thus allows evaluation of changes in frequency and characteristics of smoking patterns under different treatment conditions. Participants collected and returned cigarette butts each week, and they self-reported the number of cigarettes smoked per day [18]. We measured exhaled carbon monoxide (CO) weekly, and we collected urine samples at baseline, before and after the washout period, and at the end of the study to measure creatinine-normalized cotinine, NNAL, and VOC excretion.

## Methods

Our study protocol followed the SPIRIT (Standard Protocol Items: Recommendations for Interventional Trials) guidelines (see Multimedia Appendix 1 for the SPIRIT checklist).

### Study Setting

The study was conducted in San Diego, California, United States; participants were screened remotely by Institution A and attended the smoking laboratory facility at Institution B in person. All biologic data and other measurements were collected and analyzed at either Institution A or B.

### Eligibility Criteria

#### Inclusion Criteria

Participants met all of the following criteria: aged 21-65 years; smokers of 5 or more cigarettes per day (CPD) on 25 or more days per month for 1 year or more; smokers of Camel or Pall Mall filtered cigarettes for at least two weeks prior to enrollment, and willing to continue using this brand during the study; fluent in English; have regular telephone access; and have transportation to attend all scheduled visits. Participants must have primarily (ie, ≥50% of the time) smoked cigarettes, allowing for secondary use of other tobacco products. We verified their regular smoking status upon enrollment with an expired CO level of at least 10 ppm [19]. Because we expected to be able to detect changes in our primary outcomes at lighter levels of smoking [20,21], we included light smokers in the study.

#### Exclusion Criteria

Participants were excluded if they were currently in a smoking cessation program or participating in another clinical trial; were using nicotine replacement therapy or medication that aids smoking cessation in the past month, including Zyban (bupropion), Catapres (clonidine), Pamelor (nortriptyline), or Chantix (varenicline); or were trying to quit or reduce smoking patterns in the past month. Women who were pregnant, breastfeeding, or planning to become pregnant in the next six months were excluded. Medical exclusion criteria included any of the following:

Self-reported uncontrolled diabetes mellitus or presence of any cardiovascular issue in the past 30 days, including heart attack, stroke, severe angina (ie, chest pain), hypertension, ischemic heart disease, vascular disease, or any other cardiovascular disease.Presentation to the enrollment visit with a systolic blood pressure greater than 160 mm Hg or a diastolic blood pressure greater than 105 mm Hg, as verified by two consecutive blood pressure readings.Self-reported hospitalization for psychiatric issues.Being mentally or physically unfit to participate in the study.Current dependence on a substance other than nicotine.

### Informed Consent and Ethics Approval

Informed consent was ensured during the smoking laboratory visit by trained research assistants. All consent statements were recorded in person. Participants were informed during the consent process that they may withdraw from the study at any time for any reason. Participants were also provided with information on the purpose of the study, study objectives, and how study success will be measured. The study was approved by the Human Research Protection Program from San Diego State University (approval number HS-2018-0152).

### Intervention Description

The first week involved baseline measurements of smoking behavior and urinary biologic markers. The next 2 weeks (Weeks 2 and 3) involved filtered- or unfiltered-cigarette smoking treatments, followed by a 3-week washout period (Weeks 4-6). Week 7 involved a postwashout, repeat baseline period. The crossover condition was implemented in Weeks 8 and 9. Study cigarettes were provided during the two treatment periods (ie, 4 weeks total). ST was measured on 5 days of smoking over 8-hour periods per day during the two baseline weeks (ie, enrollment and postwashout) and during the 4 weeks of switching trials; expired CO, weight, and survey measures were assessed at all visits.

### Study Cigarettes

Two brands of cigarettes are currently available as filtered and unfiltered: Camel and Pall Mall. Participants were provided supplies of one of these two brands throughout the study period based on their preference. After baseline measurements at the beginning of Week 2, we randomly assigned participants to smoke 2 weeks’ worth of filtered or 2 weeks’ worth of unfiltered study cigarettes. We supplied study cigarettes according to the average cigarettes smoked per day for the previous week plus 10%. For example, a participant who reported smoking 10 CPD in the previous week would be provided with a supply of cigarettes that would allow 11 CPD for the entire 2-week trial. Although it is possible that changes in CPD might result from increased supplies, participants were encouraged to smoke as normally as possible and to return any unused study cigarettes in order for us to measure changes in CPD resulting from switching.

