#### Cigarettes Per Day: Self-Report and Butt Count

Standard survey questions measured how many days in the past month (enrollment [ie, baseline] visit), past week (weekly visits), and past 2 months (final visit) participants have smoked, as well as how many CPD they have smoked on those days (all study visits). In addition, participants returned their cigarette butts in a sandwich-size Ziploc bag or glass jar each week to provide a validation of their self-report. While these butts were disposed of as toxic waste in approved containers, a small portion were retained for future analyses. Previous studies have included butt counts with reliability set at 75% of returns [30]. We excluded butt count data from participants who did not return 75% of butts and provided incentive payments for returning cigarette butts at this level.

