### Sample Size

The study sample size is 40 participants, sufficient to detect moderate within-subject effect sizes (*f*=0.35) with a moderate correlation between repeated measures (*r*>0.50). This two-by-two crossover design has statistical power of 80% for a sample size of 20 in each group to detect an effect size of 10% change in average number of cigarettes smoked per day. We tried to recruit at least 10 participants of non-White ethnicities. If participants prematurely discontinued from the trial prior to crossover, we attempted to recruit replacements from the eligible pool or advertise for new participants. We recruited 20 women out of the 40 participants and randomized by sex. Sex stratification is of interest because men and women may metabolize smoke differently due to differences in body size and differences in cigarette preference and behavior. Any woman who becomes pregnant during the trial will be excluded from further participation [38].

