### Plans for Assessment and Collection of Outcomes

There were eight scheduled lab visits, each with an incentive for attendance (see Participant Retention and Complete Follow-Up section). As shown in Table S1 in Multimedia Appendix 2, these visits were to occur weekly at baseline (Week 1), during the first 2 weeks of cigarette use (Weeks 2 and 3), during the postwashout baseline (Week 7), and during the second 2 weeks of cigarette use (Weeks 8 and 9). During each visit, participants were tested for expired CO, had blood pressure and weight measurements performed, and completed surveys (see Table S1 in Multimedia Appendix 2). At Weeks 1, 3, 7, and 9, participants provided a urine sample to measure normalized cotinine and carcinogen biomarkers. All collected urine samples were stored in a –80 °C freezer. Specimens were transported from Institution B to Institution A for laboratory testing.

During visits 2-4 and 6-8, participants visited the Institution B smoking laboratory facility with their topography device, cigarette butts, and unused cigarettes (left only on Weeks 3, 4, 7, and 8). Data from the topography device were downloaded so that the number of cigarettes logged in as smoked on the CReSS device could be compared to the total number of cigarettes or butts returned, as well as the number self-reported cigarettes smoked per day. Those deemed compliant with study procedures were paid for their time and supplied with another weeks’ supply of condition-assigned cigarettes. During visit 8, the same procedure was to be followed, except that it would be the final visit and no additional study cigarettes would be provided. Due to the COVID-19 pandemic, some of these procedures were curtailed and moved to remote follow-up.

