### Oversight and Monitoring

#### Safety Monitoring Plan and Adverse Event Reporting and Harms

This study was registered at ClinicalTrials.gov (NCT03749876). A DSMB charter was established outlining the board members’ responsibilities, meeting structure, deliverables, timeline, and membership requirements. A written schedule of their individual activities, phone numbers, and copies of their informed consent forms were provided to them. The DSMB members with relevant expertise who are not involved in this study included a physician, a clinical pharmacologist, and a health behavioral scientist appointed from Institution A or from other collaborating institutions. Data on serious adverse events, including severity, outcome, and management, were included in individual participant files and in aggregate form by treatment group and were reviewed weekly. These data were provided blinded to the DSMB in a detailed report by an Institution A research assistant. Potential problems reportable to the DSMB included self-reported health issues, such as respiratory problems, addiction or dependence, or nicotine toxicity signs and symptoms. In the event of concerns, the DSMB would notify the PI, and the medical consultant was to be promptly consulted. The PI would assess the potential risks to the participant regarding continuation of the trial and report back to the DSMB on findings; the DSMB would then decide if the trial should continue or if the participant should be excluded.

Although smokers will be switching to unfiltered cigarettes for this trial, a 2-week trial period is highly unlikely to provide any differential short- or long-term risks to participants who smoke unfiltered cigarettes. The targeted cigarette brands are commercially available to the population already and, hence, do not constitute a new product test. In addition, a physician-member of the research team will be on call to answer queries from the field staff regarding problems or questions from participants regarding switching to unfiltered cigarettes.

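### Study cigarettes are supplied at previous-week consumption plus 10%, so if participants stop when the supply runs out, an increase in cigarettes per day is understated more than a decrease

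*Protocol article*

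**What the plan says.** Study Cigarettes gives the dispensing rule: "We supplied study cigarettes according to the average cigarettes smoked per day for the previous week plus 10" per cent. In its worked example a participant who reported 10 CPD "would be provided with a supply of cigarettes that would allow 11 CPD for the entire 2-week trial". The same section names one risk of the rule: "Although it is possible that changes in CPD might result from increased supplies". Its response is to ask participants to keep to their normal smoking and to hand back what they did not use.

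Sample Size states 80% power with 20 participants per sequence "to detect an effect size of 10% change in average number of cigarettes smoked per day". It gives neither a direction for that change nor a standard deviation. CPD, by butt count and self-report, is part of the second specific aim under Study Objectives.

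Plans for Assessment and Collection of Outcomes describes resupply at visits: "Those deemed compliant with study procedures were paid for their time and supplied with another" week's worth of the assigned type. It also has device-logged cigarettes compared with the returned cigarettes or butts and with self-report.

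**The concern.** The margin in the supply (10% per person) has the same size as the mean change on which the trial is sized. If mean CPD rises by 10% and individual changes spread evenly around that mean, about half of the participants would want more than they were given. Such a participant can do one of three things:

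- **Stop.** Measured CPD is held at the supply.
- **Top up with the usual filtered brand.** Everyone smoked one before entry ("smokers of Camel or Pall Mall filtered cigarettes for at least two weeks prior to enrollment"). CPD is preserved, but the unfiltered condition is diluted.
- **Buy the assigned type.** "The targeted cigarette brands are commercially available to the population already", so this is possible, and it does no harm if the extra cigarettes are counted.

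The rule applies in both conditions but binds more often where demand is higher. An increase under unfiltered cigarettes therefore shrinks more than a decrease. Handing back unused cigarettes documents smoking below the supply and is silent on running out. What is at stake is the size of an estimated CPD increase, which a pilot meant to inform a larger trial would pass on.

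**Working it through.** **Inputs from the article.** Supply margin +10% of previous-week CPD (Study Cigarettes); 10% change in mean CPD, 80% power, 40 participants (Sample Size).

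**Assumptions, not in the article.** Two-sided 5% test. Individual percentage change from baseline is normal with SD s in each condition, and its mean is 0 under filtered and m under unfiltered cigarettes. The changes in the two periods correlate at r = 0 or r = 0.5.

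**Step 1: the stated power.** No SD is given, so the 80% cannot be reproduced directly. I solved for the SD that yields it. A paired t test with N = 40 and 38 df reaches 80% at a standardised difference of 0.4546. The SD of the within-person difference is then 10 / 0.4546 = 22.0%. Since SD of difference = s√(2(1-r)), s = 22.0/√2 = 15.6% at r = 0, and s = 22.0% at r = 0.5.

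**Step 2: mean when everyone stops at the supply.** With cap c = 10 and z = (c-m)/s, the capped mean is C(m) = m - s[φ(z) - z(1-Φ(z))]. The observed contrast is C(m) - C(0), because the filtered condition is capped too.

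| | s = 15.6 (r = 0) | s = 22.0 (r = 0.5) |
|---|---|---|
| C(0) | -2.45 | -4.67 |
| C(+10) | 3.79 | 1.22 |
| C(-10) | -10.73 | -12.17 |
| True +10: observed contrast | 3.79 + 2.45 = +6.24 | 1.22 + 4.67 = +5.89 |
| True -10: observed contrast | -10.73 + 2.45 = -8.28 | -12.17 + 4.67 = -7.50 |
| Loss, increase / decrease | 3.8 / 1.7 points | 4.1 / 2.5 points |

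At m = 0 the contrast is 0. At m = +20 it is +10.0 for either s.

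**Step 3: part of the excess still smoked and counted.** If half of it is, the contrast is the average of the true and the all-stop value. For +10 this gives (10 + 6.24)/2 = +8.1 or (10 + 5.89)/2 = +7.9. For -10 it gives about -9.1 or -8.8.

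**Step 4: power by simulation at the same two SDs** (paired t, N = 40).

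| | r = 0 | r = 0.5 |
|---|---|---|
| No cap, ±10 | 80% | 80% |
| True +10, all stop | 72% | 66% |
| True +10, half of excess smoked | 79% | 78% |
| True -10, all stop | 78% | 73% |
| True +20, all stop | over 99% | 99% |
| True 0, all stop (type I error) | 5% | 5% |

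**Step 5: weekly re-basing.** If the second week's supply were recalculated from the first, someone who stopped at 110% would receive 1.1 × 1.1 = 121% of baseline, so c = 21 in week 2. For a true +10 the week-2 contrast is 8.44 or 7.65. The two-week mean is (6.24 + 8.44)/2 = +7.3 or (5.89 + 7.65)/2 = +6.8, with power about 76% or 71%. The effect is softened but remains.

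**Step 6: when it can be ignored.** If a share p = 0.10 exhausts the supply, the mean lost is s[φ(1.282) - 1.282 × 0.10] = 0.0473s, which is 0.7 points at s = 15.6 and 1.0 at s = 22. With p at or below 10% in both conditions and a common SD, the contrast cannot shift by more than this.

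**The case against.** The strongest reply is that nothing in the article makes the supply a ceiling. Participants were asked to smoke normally, they obtained their own cigarettes outside the four supplied weeks, and both types are on sale. The survey asks about cigarettes smoked, not study cigarettes smoked, so self-report and butt counts can register consumption above the supply. All of this stands. A reader might infer that measured CPD could not rise by more than 10%. The article does not support that, and how many participants reached the supply is unknown.

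Second, the two 10% figures differ in kind: one is a per-person margin, the other a group mean. With no spread between participants, a mean rise of exactly 10% would not be truncated at all. This also stands. The match in size matters only through the spread, which is assumed here.

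Third, a rule for running out may be in the full protocol or the visit materials, which are not shown. That is possible, so its absence from the article is not the point. The point rests on the dispensing rule as stated and on the fact that the only risk it names is an increased supply.

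Fourth, the consequence is small. Power falls by one or two points if half of the excess is smoked and counted. Puff measures, carbon monoxide and urinary biomarkers still inform on compensation. The article's Discussion also expects fewer cigarettes if unfiltered ones are less palatable, which is the less affected direction. This is why the point is minor. It does not remove the effect on the size of an estimated increase.

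**Conclusion.** The concern holds in a conditional form and is minor. To the extent that participants stop when the supply runs out, a CPD increase is understated more than a decrease. In the worst case, with everyone stopping, a true +10% appears as about +6.2% or +5.9% and a true -10% as about -8.3% or -7.5%; power for the increase is about 72% or 66% in place of 80%. With partial stopping the loss is much smaller. There is no bias when there is no mean difference.

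These figures rest on normal individual changes, no mean drift under filtered cigarettes, and an SD backed out of the stated power. A reader might go further and conclude that the trial is underpowered for an increase or could not detect one. That is not supported: the low power figures need every participant to stop, and a true rise of 20% would be detected with about 99% power even then, although it would appear as only +10%.

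**What to change.** For this trial, from data already collected:

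1. From dispensing, return, butt and self-report data, tabulate by condition the share of participant-weeks in which the supply was exhausted or exceeded.
2. Keep observed CPD, counting all cigarettes, as the main analysis. Add one sensitivity analysis that treats as right-censored the weeks in which the supply was exhausted and no extra smoking was reported.
3. If exhaustion is common (for example above 10% in either condition) or differs by condition, state that a CPD increase may be understated and that a null result does not exclude an increase of about 10%. Otherwise the table itself shows the issue to be negligible.

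The cost is one table, one extra model and at most one sentence. The sensitivity analysis depends on self-report, so it bounds the bias and does not remove it. Butts give limited help beyond the counts already made, because most were discarded ("While these butts were disposed of as toxic waste in approved containers, a small portion were retained for future analyses") and the article does not say whether they were counted by type.
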